## 2.5 Description of the acts and procedures added by the research

The start of the study evaluation periods (i.e. control strategy period and intervention strategy period during which SARS-CoV-2 screening will be offered by nurses) will be randomly assigned for each site following a “cluster and crossover per period” randomisation.

During the intervention strategy period, the proposal of a self-administered questionnaire will be the other procedure added by the research (see addendum 2). The questionnaire concerns SARS-CoV-2 symptoms, contagion possibilities and situations at risk of exposure, as well as sociodemographic characteristics. It was developed by the research team from other questionnaires currently used in France (SocialCov and ComCor questionnaires, Pasteur Institute) or elsewhere .

Regardless of the answers to the questionnaire, SARS-CoV-2 screening by nasopharyngeal sampling will be offered by the triage nurse (*infirmier organisateur de l'accueil*, IOA) or the nurse in the cubicle.

A multiplex PCR test for symptomatic patients or an RT-LAMP test for asymptomatic patients will be performed, according to the symptomatology reported in the self-questionnaire.

During this period, the doctor may also offer a test to the patient if he/she has not already been offered by the nurse.

After performing a test, the patient will be treated according to the circuit defined in each hospital.

In the event of a positive test, if the patient is hospitalised, his/her care will be carried out according to the circuit defined by each hospital. Non-hospitalised patients will be referred to COVISAN or the usual department for follow-up and contact tracing. In the event of a negative test, the usual emergency procedure will follow.

For patients with a positive SARS-CoV-2 test and who have not completed the DEPIST-COVID self-administered questionnaire, a subsequent telephone follow-up will be performed to retrieve their profile based on the questions in the self-administered questionnaire. Patients will be accompanied by the research staff to complete the ComCor questionnaire of the Pasteur Institute to facilitate the study of sociodemographic, behavioural factors and practices associated with SARS-CoV-2 infection.

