#### **In the event of a positive test,**

- The patient will be treated according to the circuit defined in each hospital with particular attention to the following points: awareness, isolation measures, and contact tracing/tracking.
- The research staff will ensure that the DEPIST-COVID questionnaire received at the emergency room is completed in an exhaustive manner. Patients who have not completed the DEPIST-COVID questionnaire will be contacted by telephone to complete it.
- Patients who are not hospitalised will be managed via COVISAN or the usual department for follow-up and contact tracing. The scheme will be activated as soon as possible to facilitate the transmission of isolation and transmission risk reduction measures as well as to carry out contact tracing with the testing of household members during a home visit and the search for the source by questionnaire.
- Patients will be accompanied by the research staff to complete the Pasteur Institute paper or online ComCor questionnaire (Addendum 6), depending on availability, to facilitate the study of sociodemographic factors, behaviour, and practices associated with SARS-CoV-2 infection.
- For each positive patient, the next patient with a negative test (and matched on age, sex and area of residence in the last 10 days) will be helped to complete the ComCor questionnaire.

**In the event of a negative test,** the action to be taken will follow the usual emergency procedure.

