| Offer of SARS-CoV-2 testing by the nurse or caregiver, regardless of the answer to the questionnaire                                                                                                                                                                                 | R                                                                                                               |                                                                                                                         |
| Nasopharyngeal sampling performed and result provided                                                                                                                                                                                                                                | R (In addition to usual practice, a nasopharyngeal sample RT-LAMP test is performed for asymptomatic patients.) | S
(usual practice based primarily on a SARS-CoV-2 diagnosis by PCR in hospitalised patients or symptomatic patients) |
| For patients tested SARS-CoV-2+ who have not completed questionnaires: collection of data from the DEPIST-COVID questionnaire during a telephone call.                                                                                                                               | R                                                                                                               | R                                                                                                                       |
| Assistance in completing a ComCor questionnaire from the Pasteur Institute in paper format (see addendum 6) (or online on the study site as possible), in order to facilitate the study of sociodemographic, behavioural factors and practices associated with SARS-CoV-2 infection. | R                                                                                                               |                                                                                                                         |

*S: usual practice in the context of Care; R: practice added by the Research*

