##### Secondary endpoints analyses

- The proportion of patients tested positive for SARS-CoV-2 among the asymptomatic or paucisymptomatic patients tested by nurses and that in the Paris Metropolitan area at the same period will be compared using an asymptotic Wald test.  
The proportion obtained in each emergency department will be compared to that of the department's IRIS geographical area using an asymptotic Wald test. The same comparisons will be made across the entire tested population.
- The feasibility of the testing will be described: proportion of patients who have completed the questionnaire, proportion of offered, accepted and performed tests, and notified of the SARS-CoV-2 result and staff involved (nurses, caregivers, doctors, others),
- The proportion of patients tested positive for SARS-CoV-2 among the patients tested by nurses, the proportion of asymptomatic patients among the patients tested by nurses and the proportion of asymptomatic patients among the patients tested positive for SARS-CoV-2 will be described.

|                        |              |
|------------------------|--------------|
| Study                  | DEPIST-COVID |
| Promotion/gestion code | APHP201625   |
| Study coordinator      | [name]   |

- The symptoms of patients tested positive for SARS-CoV-2 will be described in the patients completed the questionnaire.
- Exposure factors will be described using the items in the DEPIST-COVID questionnaire. Among patients tested, the exposure factors associated with the positivity of the SARS-CoV-2 test will be analysed using a generalised linear mixed model (binomial distribution or other distribution adapted to the data). The exposure factors will be considered as fixed effects and the site as a random intercept. Other fixed variables could be added to the model if appropriate.
- The sociodemographic, behavioural and practical factors of diagnosed patients associated with positive SARS-CoV-2 infection will be described for the schemes (DEPIST-COVID, ComCor) according to the types of variables (proportion, mean and standard deviation or median, Q1-Q3) and presented with their 95% confidence interval. If appropriate, the factors will also be analysed in the population of DEPIST-COVID cases (positive tested patients) and controls (negative and matched tested patients).

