| Yes                                                                                          | .                            | 426 (11.3)                     | .                                    | 30 (16.0)                   | .                                       | 396 (11.1)                  | 5.0 (0.3, 11.0)             |
| How many people currently live with you in your home?                                 | 3745                         | 2.0 [1.0, 4.0]                 | 187                                  | 2.0 [1.0, 4.0]              | 3558                                    | 2.0 [1.0, 3.0]              | 0 (0.0, 1.0)                |
| Do you have children or students in your home?                                        | 3824                         | .                              | 191                                  | .                           | 3633                                    | .                           |                             |
| Yes                                                                                          | .                            | 1474 (38.5)                    | .                                    | 84 (44.0)                   | .                                       | 1390 (38.3)                 | 5.7 (-1.3, 13.0)            |
| Have you been in contact with someone who tested positive in the last 10 days?        | 3800                         | .                              | 185                                  | .                           | 3615                                    | .                           |                             |
| Yes                                                                                          | .                            | 851 (22.4)                     | .                                    | 55 (29.7)                   | .                                       | 796 (22.0)                  | 7.7 (1.4, 14.8)             |
| Have you ever had a screening test for COVID-19?                                      | 3798                         | .                              | 189                                  | .                           | 3609                                    | .                           |                             |

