| Yes                                                                                          | .                            | 2196 (57.8)                    | .                                    | 80 (42.3)                   | .                                       | 2116 (58.6)                 | -16.3 (-23.3, -9.0)         |
| Time to prior positive test (days)                                                    | 198                          | 148.0 [70.0, 204.0]            | 6                                    | 163.0 [103.0, 222.0]        | 192                                     | 148.0 [67.5, 202.0]         | 15.0 ( not defined ) |
| How do you rate your risk of being COVID-19+?                                         | 3657                         | .                              | 176                                  | .                           | 3481                                    | .                           |                             |
| High or very high                                                                            | .                            | 651 (17.8)                     | .                                    | 51 (29.0)                   | .                                       | 600 (17.2)                  | 11.7 (5.4, 18.9)            |
| Identical                                                                                    | .                            | 1249 (34.2)                    | .                                    | 69 (39.2)                   | .                                       | 1180 (33.9)                 | 5.3 (-1.8, 12.8)            |
| Low or very low                                                                              | .                            | 1757 (48.0)                    | .                                    | 56 (31.8)                   | .                                       | 1701 (48.9)                 | -17.0 (-23.7, -9.7)         |
| Emergency department discharge status****                                             | 1328                         | .                              | 36                                   | .                           | 1292                                    | .                           | .                           |

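### Exhaustive questionnaire completion is required only after a positive test, and nothing records whether exposure answers came before or after the result, so the secondary factor models may mix the two for cases only

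*Combined protocol and SAP*

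**What the plan says.** **Default route, all patients.** In Section 6.3.3 the patient fills in the DEPIST-COVID form and gives it to the triage nurse, or to the attending nurse at the time of care. Under Section 2.5 the type of test depends on the symptoms reported in it.

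**After a positive test.** Section 6.3.3 adds: "The research staff will ensure that the DEPIST-COVID questionnaire received at the emergency room is completed in an exhaustive manner". It continues: "Patients who have not completed the DEPIST-COVID questionnaire will be contacted by telephone to complete it". Section 2.5 gives the telephone step the same limit: "For patients with a positive SARS-CoV-2 test and who have not completed the DEPIST-COVID self-administered questionnaire, a subsequent telephone follow-up will be performed". So does the chronology table in Section 6.3.6: "For patients tested SARS-CoV-2+ who have not completed questionnaires: collection of data from the DEPIST-COVID questionnaire during a telephone call".

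**After a negative test.** Section 6.3.3 says only that "the action to be taken will follow the usual emergency procedure".

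**General check.** Section 12.1 has research technicians or nurses check that paper forms are completed, whatever the result. It does not mention going back to a patient to fill gaps.

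**Analysis.** Final SAP Section 1.1, on secondary endpoints, states: "Among patients tested, the exposure factors associated with the positivity of the SARS-CoV-2 test will be analysed using a generalised linear mixed model". The later Changes to the analysis plan adds a mixed model for factors associated with new diagnoses. SAP Section 1.3 deals with missing questionnaire values but not with when or how an answer was given.

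**The concern.** In the factor models the test result is the outcome and the questionnaire answers are the covariates. Under the plan, the effort spent on obtaining a covariate depends on the outcome, and for cases part of that effort comes after the result is known. A patient who has just been told of a positive test, or the person helping with the form, may answer differently from someone who does not know. Two items are plainly open to this: "Have you been in contact with someone who tested positive in the last 10 days" and "How do you rate your risk of being COVID-19". If some case answers are post-result while negatives have no planned post-result route, a difference between the groups may partly reflect the timing of the question. Neither model has a term or restriction that could detect this. The Table E1 footnote lists being a case contact among the factors associated with new infection, so the item contributes to a stated finding.

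**Working it through.** **1. Is the order of answer and result fixed anywhere?** The form has a start time and a reading time for the test (items 29 and 30). It has no time, mode or author for the patient's answers. Test choice needs only the symptom question (item 3). The 10-day exposure items and self-rated risk are items 14 to 25, further on. A form can therefore serve for choosing the test while those items are still blank. No section requires them to be finished before the result is read.

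**2. Can completion follow the result during the visit?** Section 6.3.3 gives an analysis time of 5 to 15 minutes for RT-LAMP and 75 minutes for multiplex PCR. Section 2.1.3 puts the median emergency visit at 3 hours. On-site completion after the result is possible with either test. A telephone call at 15 ± 10 days (Section 6.1) is bound to follow it.

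**3. Reproducing the reported differences.** Inputs are from Appendix E, Table E1. The interval is the Miettinen-Nurminen score interval: the limits are the values of d at which

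z(d) = (p1 − p2 − d) / √{[r1(1−r1)/n1 + r2(1−r2)/n2] × N/(N−1)} = ±1.96,

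where N = n1 + n2 and r1 = r2 + d are the maximum-likelihood proportions under difference d.

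- Contact: 55/185 = 29.7% vs 796/3,615 = 22.0%. Difference 7.71 (1.43 to 14.78). Table E1 gives 7.7 (1.4, 14.8).
- Self-rated high or very high risk: 51/176 = 29.0% vs 600/3,481 = 17.2%. Difference 11.74 (5.41 to 18.94). Table E1 gives 11.7 (5.4, 18.9).

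**4. How many prompted answers would matter?** Assumption: k of the case Yes answers were given only because the result was known, and they are moved to No.

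| Item | k | Case proportion | Difference (95% CI), points |
|---|---|---|---|
| Contact | 0 | 55/185 | 7.7 (1.4 to 14.8) |
| Contact | 2 | 53/185 | 6.6 (0.4 to 13.7) |
| Contact | 3 | 52/185 | 6.1 (-0.06 to 13.1) |
| Contact | 14 | 41/185 | 0.1 (-5.4 to 6.8) |
| Self-rated risk | 10 | 41/176 | lower limit 0.27 |
| Self-rated risk | 11 | 40/176 | lower limit -0.24 |

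The true k is not in the documents. These are univariate differences, not results of the mixed models.

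**5. Did the step leave a trace in the data?** Completeness in Table E1, new diagnoses (n = 224) against negatives (n = 3,968):

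| Item | Cases | Negatives |
|---|---|---|
| Symptoms | 216/224 = 96.4% | 3,846/3,968 = 96.9% |
| Contact | 185/224 = 82.6% | 3,615/3,968 = 91.1% |
| Self-rated risk | 176/224 = 78.6% | 3,481/3,968 = 87.7% |

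For contact the completeness difference is -8.5 points (-14.1 to -4.0). Exhaustive completion of case forms was evidently not achieved: 224 − 185 = 39 contact answers and 224 − 176 = 48 risk answers stayed missing.

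**The case against.** The case on the other side is substantial.

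- **Staff are to ensure completeness, not to re-interview.** The instruction concerns a form already received in the department, and Section 12.1 has all paper forms checked. This is right as to wording. But Section 12.1 gives no route back to a negative patient, so the asymmetry remains.
- **The default order protects most answers.** The form is meant to be in hand when the test is chosen. This stands, and it confines the issue to answers added later.
- **The quick test gave fewer than half of the cases.** In Table E1, 108 of 224 new diagnoses came from the rapid SARS-CoV-2 test and 116 (51.8%) from the multiplex test. For the latter there was more time to finish the form before the result. This weakens the timing argument but does not remove it.
- **Cases were less complete, not more.** This stands as evidence that the step did little. It does not show that the answers which are present came before the result.
- **The tipping point only reflects a lower limit close to zero.** This is also correct: it measures fragility and is not evidence of bias.

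A reader might infer that the reported contact and risk associations are in fact inflated. The documents do not support that, since no count of late answers exists. A reader might also fill in the 39 and 48 missing case answers as mostly Yes and obtain much larger differences. Those answers stayed missing, so such a calculation does not describe bias in the reported table.

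Matched negatives are helped too, but with the ComCor questionnaire. The point does not extend to that comparison.

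**Conclusion.** The point holds as a gap in the plan. Exhaustive completion and telephone completion of the DEPIST-COVID form are specified for positives only, and neither the protocol nor the form separates pre-result from post-result answers. The factor models can therefore compare answers collected under different conditions.

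The effect on the reported results cannot be derived and may be small. Three prompted answers of 55 would be enough for the contact interval to include zero, and eleven of 51 for self-rated risk. Both figures assume that the prompted answers would otherwise have been No.

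The scope is limited to secondary, associational analyses in patients tested through the study screening, because SAP Section 1.5 says exposure data were not collected for other tested patients. The primary outcome uses none of these answers.

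**What to change.** 1. In Section 6.3.3, have items 14 to 25 completed before the test result is read wherever the patient is able.
2. On the form, record whether any answers were added after the result and by what route (patient on site, staff on site, telephone).
3. In the SAP, add a sensitivity analysis of both factor models restricted to pre-result answers, reported beside the model with all answers.

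The all-answers model should stay. Missingness already differs by outcome, so dropping late answers from the main model would exchange a possible recall bias for a possible selection bias.

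The cost is a small addition to the form, one extra analysis, and somewhat more missing case data in the restricted analysis. For answers already collected, the form does not allow the restriction. The contact and self-rated-risk results should then carry a statement that the timing of case answers relative to the result is unknown.

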#### **In both cases (positive or negative):**

- The agreement to participate in the study will be noted on page 4 of the questionnaire and/or by the nurse in the patient file.
- The time of the test and the result will be tracked on the back of the questionnaire and/or in the medical record.
- The team will send the test result to the patient.

#### **6.3.4 Control strategy**

The doctor offers a SARS-CoV-2 test according to current recommendations. At the time of writing of this project, the tests are PCR tests prescribed for diagnosis for patients presenting symptoms suggestive of Covid-19 or when screening patients who need to be hospitalised for another reason before being transferred to the hospital department (to avoid hospital clusters). The patient will be cared for according to the circuit defined in each hospital. Patients with a positive test will be asked to complete the DEPIST-COVID questionnaire. Patients who have not completed it will be contacted by telephone to answer questions by phone.

#### **6.3.5 Criteria for choosing tests**

The choice of test used is based on available data on sensitivity and specificity, on criteria for handling in the emergency department (storage, number of operations, time for reading, published experiments) and on the test supply capacities. These criteria led to the selection of the following tests with a CE marking:

1 - For patients with symptoms suggestive of respiratory infection: the test is based on a multiplex PCR technique detecting SARS-CoV-2 and all other community-acquired viral infections (Qiasat, Qiagen). This test involves performing a nasopharyngeal swab using a thin, flexible swab with a flocced nylon tip, inserting the swab into the test cassette and inserting it into the Qiasat automated PCR system, which performs all analytical steps. The result is available in 75 minutes. This test does not require any prior technical experience and can therefore be easily performed in an ED. In addition, the direct introduction of the swab into a cassette minimises the handling of an infectious sample and thus limits any risk of secondary contamination.

2 - For asymptomatic patients: an RT-LAMP (Abbott ID NOW, Abbott) test to detect the SARS-CoV-2 genome will be used.

It has several advantages:

- The technique is quick and easy to implement by staff not qualified in biology;
- It can be performed directly after sampling without handling infectious fluids;
- The result is available in less than 15 minutes, thus facilitating patient management;
- Single temperature genome amplification provides a simple and space-saving machine;
- The analytical performances (sensitivity and specificity) are close to those obtained with RT-PCR performed in a laboratory.

The RT-LAMP test is more sensitive than an antigen test and therefore more compatible with a diagnosis performed in a healthcare facility, while the antigen test is more suitable for mass testing in the outpatient department. Positive tests with the RT-LAMP technique performed in asymptomatic patients will not be confirmed by PCR.

This test is also performed using a nasopharyngeal swab. The swab is inserted into a cassette containing reagents that inactivate the virus by heating to 56°C. After inactivation, the viral genome is amplified by using isothermal nucleic acid amplification technology (NAAT) to detect the RNA-dependent RNA polymerase gene (RdRp) segment of the SARS-CoV-2. A real-time analysis

delivers a result after the start of amplification between 5 minutes for the strong positives at 13 minutes for the weak positives and negatives. The machine prints a result label with the patient identification.

